### Work package 2 (WP2)

The aim of WP2 is to determine what the main risk factors for screen-detected AAA are, using the linked dataset generated in WP1 and thus develop hypothetical targeted screening strategies.

Known and putative AAA risk factors (smoking, hypertension, hyperlipidaemia, diabetes (protective factor)) will be tested for association with screen-detected AAA to determine their potential for use as sole criteria for targeted screening. Multivariable risk prediction modelling will be used to identify a set of clinical variables that can be used as criteria for targeted screening. Predictors for inclusion in the model will be selected based on mathematical/statistical performance and no predictors will be forced into the model based on prior assumptions.

If the final model is based on a small number of variables, adaptation for clinical and public use will also be considered. The target population for the model will be the same as the population in which it is developed, ensuring the relevance of the model to future clinical practice.

The primary performance criterion for the model will be achieving a predefined sensitivity threshold for detecting true positive cases in targeted AAA screening. This success criterion and/or the success threshold may be revised depending on the outputs from ethical study and focus groups. Sensitivity analyses to test variable selection strategies will be performed and the TRIPOD checklist will be used to present overall model results [27].

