**Fig 1 pone.0327856.g001:**
[figure not shown]
Data flow diagram for data linkage between NAAASP and CPRD. NHSE – NHS England, NECSWS – NEC software solutions, SCWDSCRO – South Central & West Data Services for Commissioners Regional Office, CPRD – Clinical Practice Research Datalink, EMIS/Vision – GP software from where data derives, CAG – health research authority confidentiality advisory group.

Data from the NAAASP will cover an eleven-year period from 2013 to 2024, thus we expect to have screening records for over 2,500,000 men invited for screening and over 25,000 men with AAAs. Primary care data will be obtained from the Clinical Practice Research Datalink (CPRD). CPRD is a database of anonymised primary care medical records covering over ~19 million patients from 1927 different UK GP practices [16–19]. Coding of clinical events in CPRD has been both technically and clinically validated [20–26]. We estimate that at least 20% of men invited for screening between 2013 and 2024 will be currently registered with GP practices contributing to CPRD.

We will undertake data linkage using the CPRD’s established pathway and patient level data-flow model for non-standard linkages. For this study both CPRD Aurum and CPRD GOLD datasets will be extracted.

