The linkage will be conducted as follows (numbers in brackets refer to the numbers contained within Fig 1); (1) CPRD will instruct GP software suppliers, EMIS and Vision, to share NHS numbers and GP software (EMIS/Vision) patient pseudonyms for CPRD contributing practices with NHSE (the CPRD cohort file). (2) NHSE will share the CPRD cohort file with the South Central & West Data Services for Commissioners Regional Office (SCWDSCRO). This is an organisation within NHSE which will carry out linkage itself. (3) NAAASP via their software provider NEC Software Solutions will extract data from the NAAASP database according to a predefined data specification. (4) NAAASP will then share this extract file with SCWDSCRO. (5) SCWDSCRO will link the CPRD cohort file and NAAASP extract by NHS number, filtering and removing those men not within the CPRD cohort file. CPRD identifiers (the GP software patient pseudonyms) are added to the remaining NAAASP records. A new pseudonym is generated for each individual and the NHS numbers are stripped from the dataset. (6) This datafile is passed to CPRD. (7a) CPRD will use the GP software pseudonyms to add the CPRD patient pseudonyms to the dataset and then remove these GP software pseudonyms. (7b) CPRD patient pseudonyms are used to add the CPRD data which is added to the dataset. (7c) The whole dataset is then re-pseudonymised by creation of a new CPRD patient ID that is study specific and removal of all other pseudonym IDs except the study pseudonyms and newly generates study specific CPRD patient IDs. (8) This dataset will contain the CPRD and NAAASP linked data and is passed onto the University of Leicester. (9) University of Leicester perform study analysis.

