### Work package 3 (WP3)

Work package 3 consists of the following three tasks: Reviewing and updating an established discrete event simulation model (DES) of AAA screening, conducting in-silico trials of targeted vs population screening for AAA to determine the diagnostic accuracy of targeted screening and modelling the long-term effectiveness of targeted vs population screening using DES modelling.

In the ‘Screening Women for aortic ANeurysm’ (SWAN) project [10], a new DES model of AAA screening was developed to estimate the clinical and economic effectiveness of screening over a 30-year period [28]. The model provides outputs in terms of the number of clinical events, life-years gained with screening and incremental cost-effectiveness ratios (cost per quality-adjusted life-year gained) for a follow-up period of 30 years after screening. The model allows individual screening parameters to be varied and has been used to estimate the clinical and economic effects of varying surveillance intervals for men with small AAA in the NAAASP [28]. In this study, we will adopt the DES model to estimate the effectiveness and cost effectiveness of targeted AAA screening compared with whole population screening. We will populate the model using the data from in-silico trials.

The linked NAAASP-primary care dataset will be used to test the targeted AAA screening strategies developed in work package 2. This will conform to the following clinical trial structure:

(P)opulation: Men in the year of their 65th birthday (current AAA screening population)

(I)ntervention: Risk-factor targeted invitation for AAA screening

(C)omparison: Whole population screening

(O)utcome: Diagnostic effectiveness of targeted screening

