## Discussion

This will be the first virtual in-silico trial comparing targeted screening and population screening of AAA. The objective of the study is to assess the clinical and cost-effectiveness of targeted AAA screening, aiming to establish its viability as a solution to the declining cost-effectiveness of population-based AAA screening programs. Patient and public engagement has been central to the study from its inception and will remain integral throughout its implementation. Focus groups consisting of beneficiaries of screening and members of the public will help frame the success criteria and acceptability thresholds of the quantitative outputs, enhancing the relevance and applicability of the study’s findings.

This project’s strengths are founded on its mixed-method approach, utilization of a substantial real-world dataset (the largest linkage of national screening data to date), application of an established statistical model (DES model) combined with strong patient and public involvement. Multiple work packages provide a multimodal overview to address the research question.

Only an estimated 20% of the entire dataset will be available for linkage with primary care data, which itself has numerous inherent limitations (data incompleteness, coding variability, and selection bias). Despite this, the large sample size will have adequate sensitivity and power to develop, validate and test proposed risk stratification models. Multiple strategies may have to be employed to account for potential missing data. While multiple imputation remains one of the more widely used approaches, its appropriateness in prediction settings is debated. Multiple imputation generally assumes data is missing at random which is unlikely to be true in primary care records. Therefore, multiple imputation may introduce bias and limit generalisability. Sensitivity analyses will be essential to evaluate model performance across key subgroups and it will be important to explore if missingness itself carries a predictive value.

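### The risk model and the DES screening inputs come from the roughly 20% of NAAASP men linked to CPRD, and no comparison with or calibration to the whole programme is described

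*Protocol article*

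**What the plan says.** **Population.** Work package 2 states "The target population for the model will be the same as the population in which it is developed" and gives as the benefit "ensuring the relevance of the model to future clinical practice". Work package 3 defines the in-silico trial population as the men whom the programme currently screens, with whole-population screening as comparator.

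**Data flow.** The NAAASP extract is expected to hold "screening records for over 2,500,000 men invited for screening and over 25,000 men with AAAs". Work package 1 estimates that "at least 20% of men invited for screening between 2013 and 2024 will be currently registered with GP practices contributing to CPRD". At linkage step 5 the two files are matched, "filtering and removing those men not within the CPRD cohort file". Step 8 then reads "This dataset will contain the CPRD and NAAASP linked data and is passed onto the University of Leicester".

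**Use.** Of the DES, Work package 3 says "We will populate the model using the data from in-silico trials". The trials' secondary outcomes are the DES screening inputs: attendance, repeat invitation, failed visualisation, aneurysm size, prevalence and the share of AAAs detected.

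**Limitation.** The Discussion says "Only an estimated 20% of the entire dataset will be available for linkage with primary care data" and lists selection bias among the weaknesses of primary care data. Its reply is that the sample is large. It also promises sensitivity analyses across subgroups.

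**The concern.** The reference case is meant to be the national programme. The men who inform it are a subset selected by whether their practice contributes to CPRD and, as the estimate is worded, by current registration. If current registration governs linkage, invited men who have since died or moved practice may also be missing.

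The Background says that uptake is lower in deprived areas, where AAA is more common. An imbalance in deprivation between linked and unlinked men would therefore shift attendance and prevalence, both of which are DES inputs. The article calls prevalence the key determinant of cost-effectiveness. Work package 3 reports absolute event counts and incremental net monetary benefit, and lists predictive values, which depend on prevalence, within the primary outcome.

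A larger sample narrows intervals around whatever the linked men show; it does not bring that value closer to the programme's. Subgroup analyses within linked men cannot show how they differ from the rest.

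**Working it through.** **1. The plan's own figures.** Work package 1 gives 2,500,000 invited men, 25,000 AAAs and at least 20% linkage.
- 0.20 × 2,500,000 = 500,000 men; 0.20 × 25,000 = 5,000 AAAs. Both agree with the sample size section.
- Half-width for sensitivity p with n = 5,000: 1.96 × √(p(1−p)/n). At p = 0.70 this is 1.27 points; at p = 0.75 it is 1.20 points. Both lie within the stated ±1.5 and ±1.25.

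The sample size is sound and not at issue. Because 20% is a minimum, the 80% removed is an upper figure.

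**2. How selection enters.** Let L and U be the values of any quantity in linked and unlinked men. The programme value is 0.2L + 0.8U, so the linked-only error is L − (0.2L + 0.8U) = 0.8(L − U). The documents do not give L − U, so these values for sensitivity are assumed:

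| Assumed L − U (points) | Error of linked estimate (points) |
|---|---|
| 2 | 1.6 |
| 5 | 4 |
| 10 | 8 |

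Even the smallest exceeds the planned margin of 1.25 to 1.5 points.

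**3. Prevalence.** Assume that linked men differ from the programme by 5% to 15% in relative terms, and take the latest figure in Table 1, 0.76%.
- 5%: 0.76 × 0.95 = 0.72% to 0.76 × 1.05 = 0.80%.
- 15%: 0.76 × 0.85 = 0.65% to 0.76 × 1.15 = 0.87%.

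The whole range lies above the stated threshold region of 0.35–0.55%.

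**4. Can it be checked?** Table 1, summed over 2013/14 to 2022/23, gives 2,824,967 invited, 2,237,762 attending (79.2%) and 22,502 AAAs (1.006% of attenders). Unlinked counts follow by subtraction. With an assumed exact 20% split, the 95% half-width for linked minus unlinked is 1.96 × √(p(1−p)(1/n₁ + 1/n₂)).
- Prevalence, pooled: p = 0.01006, n₁ = 447,552, n₂ = 1,790,210; half-width 0.033 points.
- Attendance, pooled: p = 0.792, n₁ = 564,993, n₂ = 2,259,974; half-width 0.12 points.
- Prevalence, 2022/23 alone: p = 1,942/254,439, n₁ = 50,888, n₂ = 203,551; half-width 0.085 points, about 11% of 0.76%.

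A 5% relative difference from the programme is 0.05 × 1.006 = 0.050 points, or 0.050/0.8 = 0.063 points between linked and unlinked men. Pooled data would show it; a single year would show only larger differences.

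**5. What cannot be checked.** Table 1 has no deprivation, region, repeat invitation, visualisation or size-band data, and stops a year before the planned 2023/24. Unlinked men have no primary care data in this study, so their risk factors, and the sensitivity of any strategy among them, are not observable from any NAAASP summary.

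**The case against.** A reader might infer three stronger things, none of which the document supports.

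- *That selection bias can be neither checked nor corrected.* Table 1 allows attendance and prevalence to be compared and calibrated with no change to the data flow.
- *That the other men's data are lost.* Step 5 filters a patient-level linkage file. NAAASP remains the data holder, and nothing says that its summaries are unavailable.
- *That the Work package 2 sentence is false.* Linked men are invited NAAASP men, hence a sample of the target population. The fault is that representativeness is assumed and then offered as assurance of relevance.

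Other arguments go the same way. The Discussion discloses the 20% and the selection bias. It also says that the DES will be updated, including for screening compliance, without limiting the source to linked men. Representativeness tables are often left to a fuller document. The prevalence illustration crosses no threshold, and a shift in prevalence alone need not change sensitivity.

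These points limit the finding but do not remove it. The article does fix where the DES inputs come from, asserts equality of populations, and answers an admitted bias with sample size. That is a reply on the page that does not work, not detail left out for length.

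**Conclusion.** The point holds in limited form. The model and the DES screening inputs rest on about a fifth of the programme, the equivalence of that fifth to the target is assumed, and the stated answer to selection bias does not address it.

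The size is unknown. Under the assumed differences, the error in sensitivity would be 1.6 to 8 points against a planned margin of 1.25 to 1.5, and prevalence could sit anywhere from 0.65% to 0.87% instead of 0.76%. The latter changes absolute counts, costs and QALYs but does not by itself overturn the cost-effectiveness of screening. These figures assume exactly 20% linkage and differences that the documents do not report.

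The matter should be addressed because the policy claim depends on representativeness and part of the check needs only counts already published in the article.

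**What to change.** 1. Compare attendance and AAA prevalence in the linked cohort with programme-wide counts, by screening year and pooled, using Table 1 extended to 2023/24.
2. Where NAAASP can supply them, add aggregate counts, with small numbers suppressed, of repeat invitation, non-visualisation and AAA size band, by deprivation or region if recorded. The article does not say whether those two are held in the extract.
3. Standardise the linked cohort to these programme margins, and use the same standardised cohort for both the whole-population and the targeted arms of the DES. Feeding one arm from programme totals and the other from reweighted linked men would put source differences into the incremental costs, QALYs and net monetary benefit.
4. Run the unweighted linked cohort as a sensitivity analysis.
5. Reword Work package 2 to say that the model is developed in a linked sample of the target population, with representativeness checked against programme totals.
6. State as a limitation that strategy sensitivity in unlinked men is unobserved. Weighting corrects only for the variables tabulated.

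Cost: a small aggregate data request, possibly with an approvals check because Section 251 approval is already in place; modest weighting work; and slightly wider intervals. The request goes to NAAASP as data holder, so it can be made even if linkage has finished.

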### Work package 3 (WP3)

Work package 3 consists of the following three tasks: Reviewing and updating an established discrete event simulation model (DES) of AAA screening, conducting in-silico trials of targeted vs population screening for AAA to determine the diagnostic accuracy of targeted screening and modelling the long-term effectiveness of targeted vs population screening using DES modelling.

In the ‘Screening Women for aortic ANeurysm’ (SWAN) project [10], a new DES model of AAA screening was developed to estimate the clinical and economic effectiveness of screening over a 30-year period [28]. The model provides outputs in terms of the number of clinical events, life-years gained with screening and incremental cost-effectiveness ratios (cost per quality-adjusted life-year gained) for a follow-up period of 30 years after screening. The model allows individual screening parameters to be varied and has been used to estimate the clinical and economic effects of varying surveillance intervals for men with small AAA in the NAAASP [28]. In this study, we will adopt the DES model to estimate the effectiveness and cost effectiveness of targeted AAA screening compared with whole population screening. We will populate the model using the data from in-silico trials.

The linked NAAASP-primary care dataset will be used to test the targeted AAA screening strategies developed in work package 2. This will conform to the following clinical trial structure:

(P)opulation: Men in the year of their 65th birthday (current AAA screening population)

(I)ntervention: Risk-factor targeted invitation for AAA screening

(C)omparison: Whole population screening

(O)utcome: Diagnostic effectiveness of targeted screening

In-silico trials will then be run using the full range of targeted screening strategies determined in work package 2. Significant risk factors (such as smoking) will be examined as criteria for screening, both in isolation and in combination. The primary outcome for these in-silico trials will be diagnostic effectiveness (sensitivity and specificity, positive and negative predicative values, likelihood ratio, diagnostic odds ratio and area under the receiver-operator characteristic curve). Secondary outcomes will be those required to re-parameterise the DES model (re-invitations, attendance, non-visualisation, AAA size distribution at screening, AAA prevalence at screening and proportion of AAAs detected). For each screening strategy, individuals will be categorized into invited and non-invited groups. In each of these groups, the actual screening outcomes will be known and using the true detection rate the overall proportional detection rate for each hypothesized screening strategy can be calculated.

The trial outputs from each targeted screening scenario examined will be compared for their effect on long-term clinical and cost-effectiveness. Absolute numbers of clinical events for the varying screening scenarios can be calculated using the DES model and used to compare clinical outcomes using the reference case scenario of whole-population invitation for screening as a comparator. Clinical results will be presented as changes to the number of clinical events, principally proportional AAA detection and AAA mortality but including the effect of quality-adjusted life years. Outcomes will be presented as the incremental cost per quality adjusted life gained and incremental net monetary benefit (INMB) between targeted screening and whole population screening. Sensitivity analyses will be conducted to explore the key assumptions used in the model; the effect of varying the methods for calculating smoking status, hypertension and hyperlipidaemia will be examined as well as additional sensitivity analyses for coding variations in any strong predictors of AAA identified in the risk prediction modelling exercise. Additional analyses relating to the management and delivery of both AAA screening and vascular surgical services will be considered on a case-by-case basis.

### Medical ethics work package 4

Alongside work packages 1–3, a qualitative study will be run to explore ethical issues and the public acceptability of targeted screening. This will assist us with the framing of results from the project and feed into the quantitative data analyses. The key question that this work package will address is what degree of underdiagnosis is acceptable in AAA screening programmes if costs need to be reduced to maintain viability for the NHS. We will establish what particular qualities of the screening programme that the public value, and whether there is potential for stigmatisation with targeted screening approaches. This study will be used to propose success criteria for the later quantitative work packages.

This study will take place in two stages, firstly a qualitative evidence synthesis review will be undertaken to identify ethical issues associated with targeted screening and establish themes and topic guides for the second stage of this research where focus group discussions will be used to explore the ethics and acceptability of targeted AAA screening. Focus group discussions may be supplemented with individual participant interviews either to follow-up with focus group participants or with additional participants who preferred not to attend focus group meetings.

Focus groups will be undertaken with four key group types; men who have already undergone AAA screening, men who are due to be invited to national AAA screening, men who did not attend screening but were invited to screening and members of the public (including young age groups and women). There will be at least two different focus groups run for each key group type. The authors expect difficulty in recruiting more than one focus group for men who did not attend screening and thus only one focus group may be performed for this group type.

Nearing study completion, our study results will be presented to and discussed with a patient and public involvement group (PPI) in order to obtain their views on the research findings. Together, the research team and the PPI group will craft a policy approach based on the findings with the aim of developing a set of public acceptability thresholds for the diagnostic accuracy of targeted screening to take forward the outputs from the project as a whole.

### Sample size calculation

Allowing for a minimum of 20% data availability in CPRD, linked data will be available for just over 500,000 men, with over 5,000 AAA cases. We expect our most basic model of targeted screening based on smoking status alone to have a sensitivity for AAA detection of between 45% and 85% [29,30]. Our sample size of 5,000 AAA cases has adequate power to estimate sensitivities of 70% and above with a marginal error of +/- 1.5% and sensitivities of 75% and above with a marginal error of +/- 1.25% (Hajian- Tilaki method [31], α = 0.05). To develop an overall risk stratification model using primary care data (work package 2), having 5,000 men with AAA (events), we have an adequate sample size to build and validate a model with over 20 predictor variables (based on a 4:1 training:testing split) [27,28]. Recognizing that events-per-variable (EPV) thresholds have limitations and can be misleading as a sole basis for determining sample size, we have used more contemporary method of sample size estimation based on the 4-step method of sample size prediction by Riley et al [32]. Accordingly, the study will have sufficient data for the development, internal validation, and testing of the proposed risk stratification model.

